## Abstract

**Background:**

Good care and conscious, mindful parenting are the essential requirements of the early childhood period. Good care in early childhood consists of mindful handling of children’s needs like hunger, care in sickness, socio-emotional needs, safety, love and affection. Good care promotes children’s development and provides a favourable environment for learning. It’s a well-known fact that hospitalization is a stressful situation for child of any age. Play is an integral part of early childhood period which is virtually restricted in hospital settings. This study will try to explore the effectiveness of play therapy delivered in hospital settings, on early child development (ECD).

**Methods:**

This will be a randomized control trial conducted in the Paediatrics department of a tertiary care hospital in Wardha, India. The sample size will be 360 children, 180 each in intervention and control arm. The hospitalized children from intervention arm will receive customized Play Therapy sessions from trained research assistants and will be followed up at scheduled monthly home visits for one year from the date of enrolment. All children will be assessed for changes in cognitive, motor and socio-emotional development scores. The differences in development scores between intervention and control groups will be compared and effect sizes of changes will be calculated.

**Discussion:**

Implementation of play stimulation activities have been reported as useful strategies for promoting child development and good recovery during hospitalization. This trial will attempt to explore the effectiveness of play therapy on changes in child development scores of children from intervention group compared to the control group. The customized play therapy program will be adapted to paediatric inpatient settings, and attempts will be made to improve the Play Therapy kit for hospitalized children.

**Registration:**

Clinical Trial Registry of India Registration No.: C.T.R.I./2022/03/041355, dated 24/03/2022. Protocol Version: v6 Dated 04/10/2024.

## Introduction

The early childhood period is crucial, usually defined as the period from birth to eight years of age. Good care, love, affection, addressing the needs of hunger, safety, socio-emotional issues and care during sickness, etc, are essential aspects of conscious parenting that promote a positive environment during childhood. A favourable and positive environment during childhood helps provide children with the opportunities to learn and thrive. Right from birth, children get bonded to special adults and try to learn the important basic skills by copying them. The learnings from these relationships serve as a base for preparing the children for life skills.
^
1
^ It was found that globally over 200 million children fail to reach their developmental potential in the first five years due to poverty, poor health services, poor nutrition, and lack of appropriate psycho-social care.
^
2
^ Early childhood is a period of rapid development. Play and recreation are naturally an essential part of childhood and are vital to normal development. Through various play and recreational activities, children learn, try to express themselves, cope with anxiety, develop their skills and master the experiences. Play can also help learn how to adapt to and tolerate the healthcare and hospitalisation experience. Play and recreation mimic the therapy of allowing children to explore, process, and express their healthcare experiences in a safe and protected environment.
^
3
^

Hospitalisation is quite stressful for a child of any age. Even older children need their parents during a serious illness, and they cannot tolerate their absence even for a short period. They want their parents to be there when they need them and wish to be loved and missed. Play is an essential part of a child’s life and key to fostering growth and development. Toys serve as the ‘tools’ of play and help to create a more ‘natural’ environment for a child. Selection and use of appropriate toys can help to reduce the traumatic effects of hospitalisation and healthcare experiences. It also aids in the speedy recovery from the illness. Play can be integral to the hospitalised child’s care and treatment plan. Play helps to support the child by offering the opportunity for creative expression, coping, and diversion. Several studies conducted in various hospitals provide evidence that a supervised play program can effectively provide a warm and child-friendly atmosphere that can help promote the child’s growth and development. In bigger hospitals and healthcare facilities, a childcare specialist can coordinate the play therapy program provided a proper play zone, suitable materials, and playmates are available. Evidently, play is an effective way of learning for any child, and play materials, toys, and equipment serve as the’learning tools’.
^
4
^

It is a well-known fact that play is useful in accelerating the growth and development of children. In many Western countries, play therapy alleviates the stress experienced by paediatric patients and their families during hospitalisation.
^
5
^ Play can prove to be of special therapeutic value for sick children. It can help to enhance their physical and emotional well-being. It can help to explore the issues related to the child’s experiences during hospitalisation and can help to reduce the influence of negative feelings during hospitalisation. Play, blended with the treatment plan, can be quite helpful in promoting the child’s growth, development, and life skills. Healthcare professionals can incorporate play in treatment and care strategies for hospitalised children. Play can help to change the hospitalisation experience into a positive one. Appropriate activities must be chosen to help the children grow, encouraging the caregivers to bring the child’s favourite toys to the hospital and get actively involved in the procedure. Play promotes healing, improves coping potential, and helps tackle fears and express the children’s feelings. Hospitals should try to use play activities to reduce stress and convert the negative aspects of the hospital experiences into positive ones.
^
6
^

### Impact of hospitalisation on children

Hospitalization plays a significant effect in a child’s life. Many children admitted to hospitals have complex healthcare needs, and some require highly technical interventions. According to the 2013 statistics by World Health Organization (WHO), children under the age of five died from diseases like acute respiratory infections, birth asphyxia, diarrhoea, neonatal sepsis, injuries, congenital anomalies, and infant prematurity.
^
7
^ Children hospitalized with the above diseases tend to have a traumatic experience at a hospital, such as in the long-run hospitalization tends to demonstrate negative psychological and behavioural response.
^
8
^ Usually, the hospitals are focused more on physical recovery and mortality than the overall well-being of the child and her family.
^
9
^ Children tend to perceive hospitals negatively, which impacts their physical and mental health. A study found that hospitalized children felt scared, bored, and alone.
^
10
^ Children experience happiness, sadness, anger, and fear in the presence of a doctor and nurse.
^
11
^ In another study, it was found that there was a reciprocal relationship between anxiety, blood pressure, and heart rate.
^
12
^ It was also found that when children were asked to draw a person in a hospital, the drawings indicated anxiety. They drew pictures of people who were sad and dependent.
^
13
^

Furthermore, according to the parents, a child’s behaviour, function, and health before hospitalization and after hospitalization are significantly different. Children suffer from emotional distress three to five months after hospitalization and surgery, which is most common in the age range of one year to six years. Trauma that children face at the hospital has been termed Paediatric Trauma Mental Stress which is characterized by avoidance, re-experience of the event, and hyperarousal which arises from a major illness or medical Intervention that causes a threat to a child’s health and is considered to be intrusive, painful and alarming medical care. Children tend to internalize their problems and may have symptoms of depression and anxiety which further aggravates their illness.
^
14
^ Certain risk factors are involved when children are hospitalized or undergo surgery. Some risk factors may be attributed to their age range, temperament, baseline anxiety, past medical encounters, and parents’ Level of anxiety. Children tend to suffer from anxiety while hospitalized due to uncertain treatment possibilities.
^
15
^

### Play stimulation for hospitalised children

Children, when hospitalized, tend to look for activities that can keep them calm. In some instances, they look toward their parents so that they can speak to them and look toward other children with whom they can play instead of getting bored. Some children found the hospital as a place where they can explore, learn and make new friends.
^
10
^ Physical exercise, healing touch, music therapy, therapeutic massage, and health education have decreased cancer symptoms.
^
16
^ Play activities that include art have also affected children’s overall health at the hospital. In the case of infants if their parents talk to them, massage them, make eye contact, sing to them or put objects at a closer distance and the infant grabs them, shows infants bold colours, or plays games like peek-a-boo or mimicking what the child is saying can soothe the child.
^
2
^

Other activities have also assisted in alleviating the symptoms of anxiety and pain. A study found that children prefer natural landscapes with calming colours over abstract paintings with bold colours. The realistic painting paved the way for positive physiological outcomes and was used for distraction, reducing pain perception.
^
17
^ Reading also influences children’s well-being, and when caregivers read books to children when they are sick, children feel comfortable, and their emotional affiliation with the caregivers grows.
^
18
^ Videoconferencing with the family has also assisted in reducing the stress of children.
^
19
^ Surgical procedures can create anxiety in children as well as their parents. A study found that before the children went through surgery, the nurses taught them the procedures and outcome of the surgery. The nurses, as well as the children, re-demonstrated the procedure in dolls. Since they observed it, this reduced their anxiety and caregivers.
^
17
^ When children above the age of four were educated about their health, they showed lower levels of anxiety than children younger than them. When play routine was introduced to hospitalized children, a lower cortisol level in their urine was indicated.
^
20
^ Play activities can help in reducing the organic symptoms in children. The time spent at the hospital can also be shortened when children participate in activities related to play stimulation.

### Rationale

As per the census of 2011, India had a population of 1211 million, among which 164.5 million children were in the age group of 0-6 years, and 372.4 million belonged to the age group of 0-14 years, which constituted around 13.59% and 30.76% of the total population, respectively. 74% of the children aged 0-6 years reside in rural areas, whereas the rural population constitutes 69% of the total population of India.
^
7
^ In India, the hospitalization rate of children aged 1-6 years is almost doubled due to common ailments like fever and diarrhoea. In contrast, hospitalization due to non-communicable diseases and injuries has also increased greatly over the last decade.
^
8
^ The average length of hospital stays ranged between 6-15 days, depending on the type of ailment.
^
9
^

The role and value of play are greater in the case of children with life-threatening diseases, disabilities, and vulnerable situations. Several diseases and conditions require the Hospitalization of children for weeks to a month. Play therapy during hospitalization can help to restore the child’s ability to play which was discontinued due to hospital admission. It can help to manage a child’s confidence that he can continue his/her normal life inside the hospital. With this understanding of play, healthcare professionals can explore the effects of Hospitalization and disease on children and enhance their emotional development.

Acharya Vinoba Bhave Rural Hospital (A.V.B.R.H.) in Wardha is a tertiary care hospital of Datta Meghe Institute of Medical Sciences and catering to the healthcare needs of the rural population from five districts Wardha, Nagpur, Chandrapur, Yawatmal, and Amaravati. A.V.B.R.H. is a 1,500 bedded healthcare facility with a specialized Paediatric Department, dedicated Neonatal Intensive Care Unit, and Child Development Centre. This study will focus on developing a locally adapted Play Therapy Programme for hospitalized children, the sensitization of parents regarding child development, and developing a safe, harmless, and sterilizable Play Kit for hospitalized children to minimize the risk of transmission of infection from children to children or healthcare staff. An earlier preprint version of this article can be found on Research Square.
^
21
^

### Objectives

*Primary objectives:*
1.To improve the motor, language, cognitive, and social-emotional development parameters of under-five years children admitted in A.V.B.R.H. through play therapy and follow-up at scheduled monthly home visits.2.To enhance the knowledge and skills of parents on early child development and improve parent-child interactions.

*Secondary objectives:*
1.To assess the effectiveness of the dedicated Play Therapy Kit specially designed for hospitalized children.2.To provide follow-up and assessment mechanisms to parents through online mode, in case the home visits are not possible.

### Trial design

This will be a randomized controlled exploratory trial. The study participants will be randomized into Intervention and Control groups with a 1:1 ratio using block randomization.

### Study setting

This study will be conducted at the Department of Paediatrics in Acharya Vinoba Bhave Rural Hospital, Wardha, and nearby villages within a 25 K.M. radius. Wardha is the smallest district in the Maharashtra State of India.

### Eligibility criteria

*Inclusion criteria:*
1.Children admitted to the Paediatric Ward of A.V.B.R.H. aged six months to 60 months.2.Children from villages within 25 Km periphery of A.V.B.R.H.3.Parents consenting to the participation of their child in the Play Therapy Programme.

*Exclusion criteria:*
1.Seriously sick, moribund children with life-threatening conditions.2.Children in Intensive Care treatment.

The Investigator will take written informed consent from the parents of the hospitalized children. The comparator (control) group will include children from the adjoining paediatric ward on another floor and admitted during the period when interventions will not be implemented. Children from this group will receive all required treatment and nursing care except the Play therapy sessions. This will help to avoid any contamination. Baseline assessments and socio-demographic information of these children will be collected at enrolment. Follow-up home visits will be done at monthly home visits. Assessments will be done at six months and 12 months from the date of enrolment. If successful, the children from control group will receive play therapy after the trial is over.

The children and their parents signing the informed consent will be enrolled in the study. All enrolled children hospitalized in A.V.B.R.H., scheduled to stay for a minimum of three days in the hospital, will be assigned a Unique ID. Children will be allocated to intervention or control groups using a block randomization process
^
22
^
^,^
^
23
^ with age groups as the blocking variable. Intervention group will receive the play therapy sessions along with the required treatment and nursing care during hospitalization stay. Sociodemographic profile and baseline assessments will be done. Play therapy sessions will be conducted at the dedicated play area in hospital. Also, these children from the intervention area will receive the play sessions at scheduled monthly home visits.
Figure 1 shows the anticipated Consort Flow Diagram of study participants.

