### Criteria for group sessions at the hospital

The hands of parents and their children will be washed before the activities start to avoid infectious contamination. Children will be divided into two groups as below:
1.Six months to 30 months old2.31 months to 60 months.

The intervention delivery details are as below:

On first day of hospitalization, parents and children will be interacted at Paediatrics ward. Randomization will be done and the parents in intervention arm will be sensitized about Play Therapy Programme. Written informed consents of parents will be taken from those who consent for participation and will be enrolled in the programme and e-learning platform/Whatsapp group.

On second day of hospitalization, a session will be conducted at designated play area in hospital. The session will emphasize on importance of early child development, its implications; diet, nutrition and healthcare of children. This session will be followed by play interaction session on cognitive and language development.

On third day of hospitalization, a play session on motor developmental activities will be conducted. This will be followed by session on socioemotional development and activities to promote it. Relevant Documents and reading materials in local language will be shared with parents during these sessions. The enrolled children will participate in play sessions and activities till the child is hospitalized.

After discharge from the hospital, parents and children will be contacted through monthly home visits personally and if needed, through online mode (Whatapp video call/Google classroom) at monthly intervals. The home visits will be scheduled for the assessment of Home Environment and Parent-Child Interactions. The monthly sessions will be continued till one year from the date of enrolment of child in the programme. Appropriate medical and nursing care will be provided during the hospital stay. If needed, referral services will be provided during follow-up at-home visits. If Children and parents insist on discontinuing play therapy, the sessions will be discontinued for those children.

After one-year of enrollment, assessments of age-appropriate developmental milestones of children will be done either in the hospital ECD Centre or through personalized home visit to the enrolled family. Age-appropriate assessment tools will be used. Reports will be shared with parents, and follow-up instructions and meeting schedules will be shared.

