### Recruitment

Parents of children reporting to A.V.B.R.H. in the first three months (January-March 2023) will be enrolled in the trial. All participants consenting to participate in the study will be assigned the Unique ID. Using a blocked randomization process with age groups as the Blocking variable, participants will be allocated to intervention or control groups. Age groups will be:
1.Six months to 30 months2.31 months to 60 months.

All children hospitalized in A.V.B.R.H., scheduled to stay for a minimum of three days in the hospital, and their parents signed the informed consent will be enrolled in the study.

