### Assignment of interventions: allocation

All participants consenting to participate in the study will be assigned the Unique ID. Sequence generation will be done using computer generated random numbers. Using a block randomization process
^
10
^
^,^
^
11
^ with age groups as the blocking variable, participants will be allocated either to intervention or control groups.

Sequentially numbered, opaque, sealed envelopes will be used for implementing the allocation sequence.

The Principal Investigator will generate the allocation sequence, trained assistants will enroll the participants, and assign participants to intervention and control groups. The Principal Investigator will train the Research Assistants for intervention, and assessors for baseline-endline assessments, supervise the data collection process and monitor the trial implementation process. We will ensure that all adults associated with the trial have the appropriate permissions and training and criminal records check to work with children. The outcome assessors and data analysts will be blinded.

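### Controls are also defined by ward and by a period without the intervention; the period clause contradicts concurrent individual block randomisation, so the actual allocation must be stated

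*Protocol article*

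**What the plan says.** Two allocation rules stand in the protocol article.

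**Randomisation of individual children.** Trial design: "The study participants will be randomized into Intervention and Control groups with a 1:1 ratio using block randomization". Eligibility criteria: "Children will be allocated to intervention or control groups using a block randomization process", with age group as the blocking variable; Recruitment and the allocation section repeat this. The allocation section adds computer-generated random numbers and concealment: "Sequentially numbered, opaque, sealed envelopes will be used for implementing the allocation sequence". The section on group sessions at the hospital places the step on the first day of the stay: "Randomization will be done and the parents in intervention arm will be sensitized about Play Therapy Programme". Recruitment gives one window for everyone: "Parents of children reporting to A.V.B.R.H. in the first three months (January-March 2023) will be enrolled in the trial".

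**Selection by place and time.** Eligibility criteria, in the paragraph before its own randomisation statement, says that the control arm is to include "children from the adjoining paediatric ward on another floor and admitted during the period when interventions will not be implemented". The reason given is "This will help to avoid any contamination".

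The article does not say that wards or periods are randomised, that children change floor after allocation, or that the recruitment window is split into periods with and without the intervention.

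**The concern.** Under individual randomisation, every eligible child has the same chance of either arm at the moment of allocation. A control admitted while the intervention is not being delivered had no such chance: the admission date had already settled the arm. For that child the envelope decides nothing.

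Two things are at stake. The first is comparability. Differences between wards or periods in diagnosis, severity, age, staff or family background would be read as an effect of play therapy, or would hide one. The second is concealment. If floor and date reveal the arm, the person enrolling knows it before approaching the parents, whatever the envelopes contain.

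The Discussion section intends a positive result as evidence-based proof of concept for a future package. A reader has to know whether the comparison behind it is randomised, and the article supports two answers.

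**Working it through.** **1. The two rules side by side**

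| Feature | Randomisation statements | Control-group sentence |
|---|---|---|
| What decides the arm | Next envelope in the age stratum | Ward and admission period |
| When it is decided | First hospital day, after admission | At admission |
| Calendar time | One window, both arms together | A period without the intervention |
| Chance of intervention for a control | One half | None |

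- *Ward clause.* This can be reconciled if children were randomised first and controls were then placed on another floor. The article does not say so, but nothing rules it out.
- *Period clause.* This cannot be reconciled in that way. Admission comes before the first-day randomisation, so no later placement can change the period in which a child was admitted.

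**2. The plan's own figure**

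Inputs from Sample size: difference 0.5, SD 1.69, z-values 1.96 and 0.84.

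n = 2 × (1.96 + 0.84)² × 1.69² / 0.5² = 2 × 7.84 × 2.8561 / 0.25 = 179.1, rounded up to 180 per arm.

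The article's 179.37 reflects rounding of intermediate values and also leads to 180. The figure is reproduced, but it presumes two independently allocated groups and does not settle how children were allocated.

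Planned standardised effect: 0.5 / 1.69 = 0.30 SD.

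**3. How much bias would matter**

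The article gives no ward or period effect, so the bias b is an assumption. It is the difference between arms that remains after the planned analysis when the intervention does nothing, in SDs of the analysed score. With n evaluable children per arm:

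false-positive rate = P(|Z + b√(n/2)| > 1.96)

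Taking the stated 10% dropout from 180 gives n = 180 × 0.9 = 162 and √(162/2) = 9.

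| Assumed b (SD) | b√(n/2), n = 162 | Rate, n = 162 | Rate, n = 180 |
|---|---|---|---|
| 0 | 0 | 5% | 5% |
| 0.1 | 0.9 | 14.7% | 15.8% |
| 0.2 | 1.8 | 43.7% | 47.5% |
| 0.3 | 2.7 | 77.0% | 81.2% |

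The rate rises with n, so a larger trial does not help.

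**4. If only some controls were taken this way**

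If a fraction f of controls carries a shift s, the mean bias is about f × s. Half the controls with a shift of 0.2 SD give 0.5 × 0.2 = 0.1 SD, which is the 15% row at n = 162.

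**The case against.** The strongest reply is that five sections describe individual randomisation, one of them with sequence generation and concealment, and only one sentence departs from it. On that view the sentence is a loose description of how the arms were kept apart. Much of this stands. A reader might infer that the trial is simply non-randomised; the article does not support that, because it does not show which rule was carried out, and if the envelopes were followed it is the control sentence that is wrong. The ward clause alone is also no contradiction.

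A reader might further infer that arm is completely confounded with ward and period. The text says the control group will include such children, which may mean only some of them.

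It can also be said that Statistical methods plans adjusted and difference-in-differences analyses, so an unadjusted t-test is not the whole analysis. That is right, and those analyses remove stable baseline differences. They do not remove differing trajectories or unmeasured confounding. Baseline is also measured during an acute hospital stay, when case mix can affect the score.

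Finally, one might try to express the problem as a design effect. That would need an intracluster correlation the article does not give. With a single ward-period per arm, the between-cluster variance could not be estimated, so no usable correction would follow.

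What the reply does not explain is the period clause. Alternating periods inside the three-month window might be imagined, but the article neither describes nor randomises them. The CONSORT diagram was not available in the text reviewed and might show the flow; it could not make both statements true of the same child.

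**Conclusion.** The contradiction is real and lies mainly in the period clause. Non-randomisation is conditional: it follows only if the control sentence was carried out, and then for whichever controls were obtained that way. In that case arm is confounded with ward and admission period, and the planned analyses repair this only in part. A residual bias of 0.1 to 0.3 SD, which is no larger than the 0.30 SD the trial is sized to detect, would raise the false-positive rate from 5% to between about 15% and 77% with 162 per arm. These rates rest on assumed biases and on a normal approximation; they show sensitivity and do not estimate what happened. If every child was allocated by envelope, the rates do not apply and the error is one of wording. A SAP could not settle the matter, because analysis cannot restore an allocation that was not random.

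**What to change.** Recruitment began in January 2023 (Trial status), and the Registration section dates this version 04/10/2024, so by the article's own dates the planned enrolment window has passed. The remedy is therefore disclosure, labelling and analysis. Simply deleting the sentence could conceal how controls were obtained.

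1. Reconcile the sections and state how each child was actually allocated, checked against the envelope log, ward and admission date.
2. If every child was allocated concurrently by the next envelope in the age stratum, remove the ward and period sentence. If controls were housed on another floor, say that this followed randomisation.
3. If any controls were taken by ward or period, disclose this and do not call that comparison randomised. Report it as a non-randomised controlled comparison adjusted for baseline score, age, diagnosis, admission month, and ward where it can be estimated. Analyse any children randomised by envelope separately.

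The cost is wording in the first case. In the second it is a weaker design label and a little more analysis.
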